**2.0 THE PROPOSED TRIAL**

**2.1 What is the proposed trial design?** A multi-centre, blinded, cluster randomized controlled trial. Hutterite colonies will be randomized to either vaccination of healthy children with licensed inactivated trivalent influenza vaccine or to vaccination of healthy children with hepatitis A vaccine as a control. The primary outcome is laboratory confirmed influenza among high risk colony members. To control for geographic variation in influenza activity, colonies will be stratified by health region (Figure 3). **2.2 What are the planned trial interventions?**

**2.2.1 Experimental:** Healthy children aged 36 months to 15 years in the intervention colonies will be immunized with inactivated influenza vaccine (VAXIGRIP vaccine) recommended for the influenza season (, 2008-2009, 2009-2010, or 2010-2011). A 0.5 ml dose of the vaccine will be administered intramuscularly. Previously unvaccinated children who are less than 9 years of age at the time of immunization will receive a second 0.5 ml dose of the influenza vaccine four weeks following the first vaccine as per influenza immunization recommendations.

**2.2.2 Control:** As a control group, healthy children aged 36 months to 15 years will be immunized with AVAXIM  -Pediatric (hepatitis A vaccine) in a blinded manner such that the schedule of immunization of influenza will be mimicked (Tables 2A and 2B). That is, children previously unvaccinated for influenza who are less than 9 years of age in the comparison colonies will be immunized with AVAXIM-Pediatric. A 0.5 ml dose of the vaccine will be administered intramuscularly. The children will receive a second 0.5ml injection of sterile saline 4 weeks following the first vaccine to maintain blinding for the second influenza vaccine dose. To complete the hepatitis immunization schedule, children will receive a second 0.5 ml dose 12 months following the first vaccine. This will also serve to maintain the blinding for influenza vaccine in the second year. Children ≥ 9 years will receive two doses of hepatitis A vaccine 12 months a part and in the third year will receive saline vaccine. These schedules ensure that children in the control arm of the study will be fully immunized for hepatitis A. **2.2.3 Rationale for choice of control:** The hepatitis A vaccine is well tolerated and will provide a potential health benefit as well as an adequate control for the study. We are aware of at least one recent outbreak of hepatitis A in a Hutterite colony and given the communal lifestyle rapid spread would be expected. An important reason why we selected hepatitis A vaccine as a control (as opposed to saline alone) is that participation in either study arm may potentially confer benefit to participants. Our experience in the pilot study suggests that this was a key factor in willingness of the Hutterites to participate. This also appeals to local public health units who are aware of risks of hepatitis A among Hutterites. Hepatitis A vaccine was used as a control in a CDC influenza vaccine trial in daycare children (17). **2.3 What are the proposed practical arrangements for allocating participants to trial groups?**

**2.3.1 Allocation:** A statistician in the Department of Clinical Epidemiology and Biostatistics at McMaster University who is independent of the study will assign colonies at random within each of eight health regions to one of the two study groups (influenza or hepatitis A), in a 1:1 ratio. For each stratum, random permutations will be generated using a SAS random number generator, with the starting number taken independently for each stratum. The statistician will keep a copy of allocation status of the colonies and forward the codes to Sanofi Pasteur in Toronto where 0.5ml pre-loaded syringes of study vaccine will receive coded study labels to allow for blinding.

**2.3.2 Stratification:** A review of the available data (from 1999-2000 to 2005-2006) shows marked differences in activity between the eight study health regions in the three study provinces (28). Influenza rates within colonies are potentially highly correlated to regional activity. Based on recommendations from experienced virologists in the study public health laboratories familiar with inter and intra-regional patterns and feasibility, we will group study colonies by health region and then randomly allocate colonies within these strata to the intervention or the control group. In addition to controlling for potentially important differences in exposure to influenza, this will also allow us to assess heterogeneity of the effect of the intervention across health regions.

**2.4 What are the proposed methods for protecting against other sources of bias?** To reduce the possibility of selection bias, the allocation of intervention or control status to colonies will occur after ~~high risk~~ participants have been enrolled in the study. This will reduce the possibility for differential consent or recruitment, or differential application of inclusion or exclusion criteria (29). Since the identity of the study vaccines will only be known to a McMaster statistician independent of the trial and to the Scientific Director of Influenza Vaccines at Sanofi Pasteur, the investigators, the study coordinator, vaccinators, outcome assessors, and data and safety monitoring board will remain blind to allocation status. The volume in influenza and hepatitis A study vaccines and saline will be 0.5 ml. Sanofi Pasteur will provide pre-filled syringes with AVAXIM-Pediatric, VAXIGRIP, and saline or diluent. The preloaded syringes will be appropriately coded as study vaccine and masked using study labels. Given that the schedule is dependent on age, there will be two schedules for each study arm (< 9 years and ≥ 9 years) (Tables 2A and 2B). Each pre-filled syringe used in the study will be identified by a numerical code that will include 1) a number from 1 to 60 that represents the colony where it is to be administered, 2) the age category (< 9 years or ≥ 9 years) of children who will receive the vaccine, 3) a dose number reflecting one of the four doses given to children < 9 years over the three year study period or the three doses given to children ≥ 9 years. This method of coding will allow us to track the study vaccines given to children without knowing the identity of the study vaccine since we will be blind to allocation of colony to study group. .

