**2.5 What are the planned inclusion/exclusion criteria?**

**2.5.1** **Colonies:** The study population will include Dariusleut Hutterite colonies in Alberta and Saskatchewan as well as Schmiedeleut colonies in Manitoba. Dariusleut and Schmiedeleut Hutterites, although belonging to different sects, are identical with respect to lifestyle and communal living. A colony is eligible if the two following criteria are met:1) The colony is within a 150 kilometer radius of designated cities or towns (Figure 4), 2) The colony has ≥10 members at high risk for complications of influenza. We selected the first criterion because 1) it increases the chance that influenza will be introduced into the Hutterite colony (i.e. the colony is not excessively isolated), 2) based on our pilot study, it is not feasible for research nurses (who live in cities and towns) to travel more than 150 kilometers to reach their first colony, 3) it reduces the number of public health regions involved, facilitating the process of communication as well as developing memoranda of understanding for vaccine depots. The second criterion allows us to assess the effect on high risk participants although the primary analysis will be conducted on all colony members. A colony will be excluded if either one of the following applies: 1) children do not receive any routine vaccinations, 2) local public health policy is to offer influenza immunization to persons beyond a high risk child’s (e.g. child with cystic fibrosis) household. As shown in Figure 3, we have already assessed eligibility criteria of study colonies.

**2.5.2 Participants:** There are two sets of participants in this trial:

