**A. Hutterites other than the healthy children who will be immunized**. Although this category as a whole will be used to assess indirect benefit of the vaccine in the main analysis, Hutterites **at high risk for influenza complications** within this category will be assessed in a separate analysis. These are defined as anyone in one or more of the following groups: individuals aged ≥ 65 years, children **23 months of age or less**, **anyone** **with ≥ 1 of the following conditions severe enough to require regular medical follow-up or hospital care: chronic cardiac or pulmonary disorders (including bronchopulmonary dysplasia, cystic fibrosis, and asthma) diabetes mellitus and other metabolic diseases, cancer, immunodeficiency, immunosuppression (due to underlying disease and/or therapy), renal disease, anemia, and hemoglobinopathy, any condition that can compromise respiratory function or the handling of respiratory secretions or that can increase the risk of aspiration.**  **There are no exclusion criteria for this category of participants.**

**B. Healthy children aged 36 months to 15 years who will be immunized as part of the intervention**. Exclusion criteria include: a) anaphylactic reaction to a previous dose of influenza vaccine, b) anaphylactic reaction to hepatitis A vaccine, c) anaphylactic reaction to neomycin, d) **known IgE-mediated hypersensitivity to eggs manifested as hives, swelling of the mouth and throat, difficulty in breathing, hypotension, or shock, e) Guillain-Barré syndrome within eight weeks of a previous influenza vaccine.**

**2.5.3 Immunization of high risk participants:** The public health units have requested that we make it clear to the Hutterites that we are only immunizing healthy children in this trial and to distinguish this from efforts of public health units to immunize high risk individuals. Therefore, we will not immunize high risk participants in this study.

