**2.8.1 Primary outcome:** The primary outcome of this study will be laboratory-confirmed influenza infection among Hutterite colony members other than the healthy children immunized as part of the intervention. We will also determine laboratory-confirmed influenza among the immunized healthy children and will assess Hutterites at high risk for complications of influenza in a separate analysis. This primary outcome is the most appropriate because the purpose of the study is to assess whether immunizing children reduces transmission of influenza to other colony members. Signs and symptoms of influenza are non-specific and cannot be differentiated from those of over respiratory viruses (30). Because non-influenza viruses circulate at the same time as influenza, clinical outcomes may be less responsive to the intervention and do not directly address the main study question. **2.8.2 Secondary outcomes:** In additionto laboratory-confirmed influenza, we will measure the following outcomes in all participants: influenza-like illness, courses of antimicrobial prescriptions, physician-diagnosed otitis media, school or work related absenteeism, physician visits for respiratory illness, lower respiratory infection or pneumonia, hospitalization for lower respiratory infection or pneumonia, all cause hospitalizations, deaths due to lower respiratory infection or pneumonia, all-cause deaths.

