
**2.11 What is the proposed sample size and what is the justification for the assumptions underlying the power calculations?** In our pilot study 8 of 57 (14%) participants had a greater than four fold rise or decline in titres (see section 1.3.7) due to either a non-vaccine strain or due to a vaccine strain in persons who were not immunized. Although previous studies that have included both viral culture and serology demonstrate that infection rates vary, an estimate of 10%is in keeping with overall community rates for years where either H3N2 or H1N1 predominate (8,9). We will test whether > 70% level of immunization can, over single influenza seasons, reduce the rate of laboratory confirmed influenza infection from 10% to 5%. If the proposed clinical trial was conducted by randomizing individuals and not clusters, 474 participants in each arm would be needed to have 80% power to detect a 50% reduction in influenza (assuming a baseline attack rate of 10%, a risk reduction of 0.50 (5%), , and type 1 error of 0.05). To adjust for the effect of within cluster dependency, a variance inflation factor is calculated using the equation 1 + (m-1), where m=average size of the cluster (per cluster=50) and = the intracluster correlation coefficient (ICC). ICCs for cluster randomized trial are seldom accurately predicted (39). Furthermore, there is little data on Hutterite colony attack rates as these are not collated by the health regions. Therefore, as recommended (39), we show in Table 3 sensitivity analysis demonstrating the power that can be achieved using a sample size of 60 clusters (the number of colonies needed to address the study question) and the range of ICCs commonly reported in cluster randomized controlled trials. We have assumed a cluster size of 50, which is the typical number of individuals in colonies interested in participating in the study. Table 3 demonstrates that with a sample size of 60 clusters we will be adequately powered to detect a difference over the range of ICCs commonly reported for cluster randomized controlled trials, 0.01 to 0.05. The table also demonstrates that our sample size allows us to assess a 50% reduction in the primary outcome assuming baseline event rates as low as 8% within a range of ICC from 0.01 to 0.04. This equates to a sample size of 1500 participants in each group. For the other comparisons that we plan to assess, sensitivity analysis shows adequate power to assess differences between study groups. For example, for testing the indirect benefit to high risk participants, for 15 high risk participants per colony, enrolling 60 colonies would give 84% power to detect a 50% reduction in laboratory-confirmed influenza (including serology which will increase the baseline event rate) from 12% to 6% between groups assuming an ICC is 0.04 and one sided alpha. The sample size has ≥ 90% power (two sided test, 60 clusters, 50 participants per cluster, ICC of 0.04) to detect the following absolute reductions: 12% to 6% for influenza-like illness, 11% to 5% for antimicrobial prescriptions, 6% to 2% for physician visits, 25% to 16% for children with otitis media, 0.7 versus 0.4 days of absenteeism (22, 40). Rates of hospitalization for participants ≥ 65 years and 6 months to 24 months will be much lower, estimated to be between 1.5 per 1000 individuals per season (13, 14). We acknowledge that for this outcome, along with pneumonia and deaths, the sample size may not be sufficient to detect differences. Nevertheless, we anticipate these data will show trends towards differences and the confidence intervals will help establish whether clinically important effects benefits are plausible with the intervention.

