**2.16 What is the proposed type of analyses?** We propose assessing whether immunizing children in Hutterite colonies with inactivated influenza vaccine can reduce transmission of laboratory-confirmed influenza to other members of the Hutterite colony. As secondary objectives, we will also assess if the intervention reduces laboratory-confirmed influenza in the high risk participants specifically and also in the immunized children. To compare mean colony differences in laboratory confirmed influenza infection between influenza and hepatitis A groups, we will use an analysis appropriate for cluster-randomized trials, namely, a t-test weighted by an inverse binomial variance weight for binary outcomes (41). We will use a similar approach for other binary outcomes. We will use a t-test weighted by an inverse variance for continuous outcomes, such as days of absenteeism. These weights are proportional to the inverse of the variances of the cluster (Hutterite colony participants) proportions or means. All outcomes will be analyzed on an intention-to-treat basis. We will also determine differences in influenza-like illness and other secondary outcomes between intervention and comparison colonies using weighted t-tests. To avoid lack of independence associated with counting multiple outcomes, each specific outcome in a participant will only be counted once in the analysis for that influenza season. The rationale for repeating the trial over several seasons is to increase the chance that there will be sufficiently active influenza season to assess the immunization strategy and also to ensure a match between the vaccine strain and a circulating strain. The trial will continue over the three years even if there is a good match the first or second year. This will allow us to determine consistency of the effect from season to season. Given annual differences in circulating influenza strains, data from each influenza season must be analysed within the context of whether there is a match or not. A match will be defined when at least one antigen in the vaccine is the same as the predominant influenza isolate that is circulating in the study regions. If there are matches in two or more years but with different antigens, then the results will be analysed separately. The interpretation will be an assessment of the consistency of the intervention i.e is the effect of immunizing children the same in matched years regardless of the vaccine antigen. If there are two or more matched years where the vaccine antigen in those years is the same, then the results will be analysed together. To do this we will conduct a repeated measures analysis of variance. That is, colony rates of influenza will be modeled by intervention group (main effect), colony effect will be nested within the intervention or comparison group, and study year will be included in the model as a covariate. If there are two strains circulating at high or equal levels, this will be taken into account in the analysis with the infections caused by both combined. The primary set of analyses will be to assess the effect of the intervention on laboratory-confirmed influenza. For the secondary outcomes, the analyses will be repeated for each outcome, including rate comparisons. Using multi-level regression modeling, we will use rates of laboratory-confirmed influenza in participants as the dependent variable, and will include random effects for a colony variable and for the health region. Variability in vaccine uptake from colony to colony will be taken into account as a fixed effect. There will be fixed effects for individual immunization and study group. This will be done for all three participant groupings (Hutterites other than healthy children, healthy children, high risk participants. We will conduct similar analyses using secondary outcomes as the dependent variable, and will also include fixed participant level variables including age, sex, and co-morbidities since these may have a prognostic effect on influenza complications. As described above, we will combine analyses in matched years if the antigen is the same but will not combine the analyses if there are matched years but different antigens each year. In terms of interactions, we will explore sex-related differences in infection rates, on the basis of whether women’s role in care for children increases risk for infection. If appropriate (skewed data) we will also conduct the analysis using non-parametric testing.

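### Section 2.1 places the primary outcome in high-risk colony members, contradicting section 2.8.1, and the power in Table 3 does not hold for that group

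*Protocol*

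**What the plan says.** The protocol describes the population for the primary outcome or primary analysis in several places.

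- Section 2.1, the design summary: "The primary outcome is laboratory confirmed influenza among high risk colony members".
- Section 2.8.1, headed as the primary outcome: "laboratory-confirmed influenza infection among Hutterite colony members other than the healthy children immunized as part of the intervention". It gives a reason for this choice and sends high-risk members to a separate analysis.
- Section 2.5.1, explaining why a colony needs at least 10 high-risk members: that criterion serves the high-risk assessment, "although the primary analysis will be conducted on all colony members".
- Section 2.5.2 A, on members outside the vaccinated group: "this category as a whole will be used to assess indirect benefit of the vaccine in the main analysis", with high-risk members assessed separately.
- Section 2.16: "we will also assess if the intervention reduces laboratory-confirmed influenza in the high risk participants specifically and also in the immunized children", introduced as secondary objectives.
- Section 1.2 lists other colony members as objective 1 and high-risk participants as objective 2. Section 2.18 calls the high-risk comparison the major subgroup analysis.

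Power is given for two populations. Table 3 uses 60 colonies of 50 participants, two-sided 5%, and states 99%, 96%, 91%, 85% and 80% for 10% versus 5% at ICC 0.01 to 0.05. Section 2.11 then turns to the other planned comparisons and states 84% for high-risk members: 15 per colony, 12% versus 6%, ICC 0.04, one-sided.

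**The concern.** A protocol should name one primary population. Here the design summary, where many readers look first, names a different one from the section that defines the outcome.

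The two differ greatly in size. In Table 1 there are 1323 high-risk members among 1323 + 3526 = 4849 members outside the healthy-child group, which is 27%. They are 20% of all 6607 eligible participants. A power statement for one group therefore need not hold for the other.

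The wording in 2.5.1 raises a separate problem of meaning. Read literally, it brings in the healthy children who receive the study vaccines (1758 eligible in Table 1). The result would then combine direct protection of vaccinees with the indirect protection that the trial is designed to isolate, and a difference could arise from the vaccinated children alone.

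**Working it through.** **Which population the text supports**

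| Section | Population | High-risk members |
|---|---|---|
| 1.2 | other colony members (objective 1) | objective 2 |
| 2.1 | high-risk members | primary |
| 2.5.1 | all colony members | assessed as well |
| 2.5.2 A | members other than vaccinated children | separate analysis |
| 2.8.1 | members other than vaccinated children | separate analysis |
| 2.16 | other colony members | secondary objective |
| 2.18 | not stated | subgroup |

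Only 2.1 makes high-risk members primary.

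**Power: inputs.** 60 colonies allocated 1:1 (30 per arm; sections 2.3.1 and 2.11); m = 50 per colony (Table 3) or 15 high-risk per colony (2.11); ICC ρ from 0.01 to 0.05; rates 10% versus 5% (Table 3) or 12% versus 6% (2.11, high-risk).

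**Formulas.** Design effect DE = 1 + (m − 1)ρ. Effective number per arm n = 30m / DE. SE = √{[p₁(1 − p₁) + p₂(1 − p₂)] / n}. Power = Φ(|p₁ − p₂| / SE − z), with z = 1.960 two-sided or 1.645 one-sided at 5%.

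**Step 1: reproduce Table 3 (m = 50, ρ = 0.04).** DE = 1 + 49 × 0.04 = 2.96. n = 1500 / 2.96 = 506.8. SE = √(0.1375 / 506.8) = 0.01647. Power = Φ(3.035 − 1.960) = 85.9%, against a stated 85%.

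**Step 2: the 2.1 population at the same rates (m = 15, ρ = 0.04).** DE = 1 + 14 × 0.04 = 1.56. n = 450 / 1.56 = 288.5. SE = √(0.1375 / 288.5) = 0.02183. Power = Φ(2.290 − 1.960) = 62.9%.

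Over the whole ICC range, 10% versus 5%, two-sided:

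| ICC | Table 3 states | Recomputed, m = 50 | High-risk, m = 15 |
|---|---|---|---|
| 0.01 | 99% | 99.0% | 76.4% |
| 0.02 | 96% | 96.0% | 71.5% |
| 0.03 | 91% | 91.4% | 67.0% |
| 0.04 | 85% | 85.9% | 62.9% |
| 0.05 | 80% | 80.3% | 59.2% |

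**Step 3: the protocol's own high-risk rates (m = 15, ρ = 0.04, 12% versus 6%).** SE = √[(0.1056 + 0.0564) / 288.5] = 0.02370, and 0.06 / 0.02370 = 2.532. Two-sided power = Φ(2.532 − 1.960) = 71.6%. One-sided power = Φ(2.532 − 1.645) = 81.2%, against a stated 84%.

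**Step 4: sensitivity.** A t-based version with 58 degrees of freedom lowers these figures by about one point. With all 1323 / 72 = 18.4 eligible high-risk members per colony enrolled, power at 10% versus 5% is about 64% to 83%. At 12% versus 6% and ICC 0.04 it is then about 76% to 77% two-sided and 85% one-sided. The stated 84% would thus need more than the 15 per colony that section 2.11 specifies.

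**Step 5: all colony members.** With 6607 / 72 = 91.8 per colony and the same 10% versus 5%, power is about 85% to 99.9% over the ICC range, no lower than in Table 3.

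**The case against.** The strongest reply is that the protocol does settle the matter. The section written to define the primary outcome names one population and justifies it. The objectives, the participant definitions, the analysis section and the subgroup section all fit it. Section 2.11 lists the high-risk power among the other comparisons. In section 2.4 the words for high risk appear struck through before the word for participants, which suggests an older high-risk focus that was not fully edited out. That last step is an inference, but it fits. In 2.5.1 the phrase about all colony members is a subordinate clause set against high-risk participants, so it most naturally means more than the high-risk group alone.

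Most of this stands, and it rules out two stronger readings that a reader might infer. One is that the trial has three rival primary populations and no single primary test. The text does not support that: 2.1 is the outlier and 2.5.1 is loosely worded. The other is that the stated power fits only one of the three populations. Step 5 shows otherwise. Table 3 fails only for high-risk members, although the protocol does not justify the 10% and 5% rates for a population that includes vaccinated children.

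It is also fair to say that 10% versus 5% is not the contrast the protocol uses for high-risk members. The 72% at 12% versus 6% is therefore the more relevant figure for that group.

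The reply does not remove the contradiction. The sentence in 2.1 is current text, it is unqualified, and it concerns the primary outcome.

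**Conclusion.** The contradiction is real and should be corrected. Section 2.1 conflicts with 2.8.1 and with every other section that ranks the analyses, and the wording in 2.5.1 should be tightened.

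If 2.1 were followed as written, the primary test would have about 72% two-sided power at the protocol's own high-risk assumptions, and about 59% to 76% at the Table 3 rates. Independently of that conflict, the stated 84% for high-risk members does not reproduce from its stated inputs: the result is about 81% one-sided.

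This does not show that the trial is underpowered for the outcome defined in 2.8.1, where the 10% versus 5% rows of Table 3 reproduce within one point.

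The figures assume 30 colonies per arm, equal colony sizes, the normal approximation, and a 5% level for the one-sided calculation, for which section 2.11 does not restate a level. They also take 50 per colony as the 2.8.1 population. Table 1 gives 4849 / 72 = 67.3 such members per colony, so 50 corresponds to about 74% enrolment, an assumption the protocol does not state.

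**What to change.** 1. In section 2.1, replace the primary outcome sentence with the 2.8.1 definition: laboratory-confirmed influenza in colony members other than the healthy children vaccinated in the trial.
2. In section 2.5.1, replace the reference to all colony members with the same population.
3. State once that the high-risk and healthy-child analyses are secondary, and use that label throughout.
4. In section 2.11, restate the high-risk power as about 72% two-sided (or about 81% one-sided) for 15 per colony, 12% versus 6% and ICC 0.04. The two-sided figure is preferable because Table 3 is two-sided.

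The cost is a few sentences, with no change to the number of colonies, the randomization or the analysis method. While editing, check Table 5 against the chosen population: it marks the pre-season, mid-season and end-of-season blood draws for the high-risk group, whereas section 2.9.2.3 assigns serology to the wider group of other members.
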